## **7-2. Secondary Endpoints**

**7-2-1. Relapse-free survival (RFS)**

1) Definition

The period from the enrollment date to the date of the first event confirmation.

2) Event definition

An event is defined as an instance of any of the following:

(1) Recurrence

(2) Death from any cause

Surviving subjects not deemed to exhibit cancerous lesions other than recurrences will be determined to have no cancerous lesions as of the final monitoring date.

**7-2-2. Overall survival (OS)**

1) Definition

The period from the enrollment date to the date of patient death from any cause.

2) Event Definition

An applicable event is defined as an instance of any of the following:

Patient death from any cause; in the case of surviving subjects, the last confirmed date of survival, and in the case of the non-traceable subjects, the last confirmed day of survival before becoming non-traceable.

**7-2-3. Adverse event onset rate and severity (safety evaluation)**

The incidence of adverse events was evaluated. Evaluation of adverse events is performed according to Japan Clinical Oncology Group/Japanese Society of Clinical Oncology (JCOG/JSCO) version of the Common Terminology Criteria for Adverse Events (CTCAE) v3.0.

**7-2-4. Drug adherence assessment**

Oral compliance during treatment is evaluated by the ratio of the amount of drug per unit time (Individual Dose Intensity: IDI) per unit time to the actual dose per actual administration period. However, IDI is defined as follows using the prescribed administration period and the scheduled dose:

- IDI = (actual total dose/actual administration period)/(expected total dose/scheduled administration period)

The scheduled administration period and the scheduled dose are defined as shown in the table below for Group A and Group B, respectively.

|  | Group A | Group B |
| --- | --- | --- |
| Planned dosage | 1 dose of capecitabine based on body surface area×2×planned treatment period (1 course)×14 | |
| Planned dosing period | 24-week period  (8 courses) | 48-week period  (16 courses) |

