# **1. Study Objectives**

The purpose of this study is to determine the optimal dosing period of capecitabine as postoperative adjuvant chemotherapy in cases of Stage III (Dukes’ C) colorectal cancer and sigmoid colon cancer involving curative resection by comparing patients receiving 8 courses (approximately 6 months) of the standard-of-care therapy consisting of capecitabine administered in a 2 weeks on, 1 week off schedule (Group A) with patients receiving 16 courses of capecitabine (approximately 12 months) on the same dosing schedule (Group B).

Primary Endpoint:

Disease-free survival (DFS) period

Secondary Endpoints:

(1) Relapse-free survival (RFS) period

(2) Overall survival (OS) period

(3) 2-year DFS rate

(4) Adverse event frequency and severity

(5) Treatment compliance

(6) HRQOL (Health-related Quality of Life)/Medical Economy　*Tertiary study conducted by capable study sites

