**5-3-2. Group B: Study treatment group (16 courses [approx. 12 months])**

Capecitabine (Xeloda tablets): Patients will receive the established dosage of capecitabine (1,250 mg/m2) based on their total body surface area (1,500 mg–2,400 mg) twice daily (after breakfast and within 30 minutes after dinner) for 14 days continuously followed by a 7-day off period. This 3-week period will comprise 1 course of treatment. Patients will receive 16 courses in total.

After completing all 16 courses, patients not exhibiting cancerous recurrence will undergo continuous monitoring without additional treatment.

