## **8-3. Secondary Endpoint Analyses**

1) DFS, relapse-free survival (RFS), and overall survival (OS) are evaluated using the same analysis.

2) An estimate of 2-year DFS rate is derived from the DFS Kaplan-Meier curve.

3) Adverse events are tabulated for each group, and the onset frequency of adverse events in the standard treatment group and the test group will be compared. However, no hypothesis testing will be conducted.

4) Drug adherence is calculated based on the rate of individual drug adherence and actual dosage per actual administration period, and is compared between the groups.

5) Summary statistics regarding total treatment costs will be estimated and compared between the groups. However, no hypothesis testing will be conducted.

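### The only defined compliance measure, IDI, is a dose rate while on treatment, so it does not reflect early stopping in a trial whose arms differ only in treatment length

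*Protocol*

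**What the plan says.** Section 1 lists "5) Treatment compliance" among the secondary endpoints. Section 7-2-4 gives the one formula for it: "IDI = (actual total dose/actual administration period)/(expected total dose/scheduled administration period"). Its table sets the planned dosage, for both groups, as "1 dose of capecitabine based on body surface area×2×planned treatment period (1 course)×14". The planned period is a "24-week period" (8 courses) in Group A and a "48-week period" (16 courses) in Group B.

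Section 8-3 states the analysis: "Drug adherence is calculated based on the rate of individual drug adherence and actual dosage per actual administration period, and is compared between the groups". The protocol defines neither the individual adherence rate named there nor the actual administration period.

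The schedule for Group B is in section 5-3-2: "for 14 days continuously followed by a 7-day off period. This 3-week period will comprise 1 course of treatment. Patients will receive 16 courses in" (quotation cut short here). Section 5-3-1 gives Group A the same course, 8 times.

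Other sections collect what the formula leaves out. Section 6-2 records start date, daily dose, days of medication and missed or reduced doses for each course. Section 6-5 records the last dosing day, the date of the decision to stop and the reason. Section 14 monitors termination status.

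**The concern.** The two arms receive the same drug at the same dose on the same schedule. Duration is the only contrast. Section 8-4 assumes equal hazards for the first 6 months after randomization, with any DFS difference appearing later. The compliance question that bears most on the primary result is therefore whether Group B patients started courses 9 to 16 and stayed on them.

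IDI divides a rate by a rate. It falls with dose reductions, missed doses and delays, but not with stopping as such. Early stopping is foreseeable: Table 3 ends protocol treatment at a fourth Grade 2 onset, a third Grade 3 onset or any Grade 4 event, with onsets counted across different events of the same grade. Group B has twice as many courses in which to reach those limits. The planned comparison could report equal compliance where much of the extra treatment was not given.

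**Working it through.** **Inputs.** One course is 14 days of two single doses a day, then 7 days off (sections 5-3-1 and 5-3-2): 2 × 14 = 28 single doses per 3 weeks. The planned-dosage cell in section 7-2-4 is read as covering all planned courses. Taken literally as one course's dose spread over 24 or 48 weeks, a full-dose patient would score 8 in Group A and 16 in Group B, which cannot be intended.

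**Planned figures reproduced.** 8 × 3 = 24 weeks and 16 × 3 = 48 weeks, as stated. Planned dose is 28 × 8 = 224 single doses in Group A and 28 × 16 = 448 in Group B. The planned rate is 224/24 = 448/48 = 9.333 single doses per week in both arms.

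**IDI after k full, on-time courses.**
- Rest week counted (actual period 3k weeks): IDI = (28k/3k)/(28/3) = 1.00 for every k, in either arm.
- Period ending at the last dose (3k − 1 weeks): IDI = 3k/(3k − 1).

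| Full courses taken | IDI, rest week counted | IDI, to last dose | Share of planned dose, A | Share of planned dose, B |
|---|---|---|---|---|
| 1 | 1.00 | 3/2 = 1.50 | 12.5% | 6.25% |
| 4 | 1.00 | 12/11 = 1.09 | 50% | 25% |
| 8 | 1.00 | 24/23 = 1.04 | 100% | 50% |
| 16 | 1.00 | 48/47 = 1.02 | – | 100% |

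On the last-dose count the earliest stopper scores highest. Full completers also differ by arm, at 1.04 in Group A and 1.02 in Group B.

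**What does lower IDI.** With the rest week counted, a Group B completer at full dose with three one-week delays scores 48/51 = 0.94. A completer at 80% dose scores 0.80. Both rank below a patient who took one full course and stopped.

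**Limits.** The score of 1.00 needs courses taken in full. A patient who takes 75% of course 1 and stops has 21 doses: (21/3)/9.333 = 0.75 with the rest week counted, or (21/2)/9.333 = 1.125 to the last dose. One who stops on day 7 has 14 doses: 0.50 over 3 weeks, or 1.50 over 1 week.

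**Group means (illustrative assumptions).** Suppose a share s of Group B stops after 8 full courses and the rest complete all 16. Mean IDI is 1.00 for any s, with the rest week counted. Mean share of planned dose is 1 − 0.5s, which is 85% for s = 30% and 75% for s = 50%.

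**The case against.** Four points can be made for the plan.

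- **IDI is a legitimate measure of intensity while on treatment, and section 7-2-4 limits itself to compliance during treatment.** This stands, and IDI should be kept. But it is the only measure defined for the endpoint, and in a duration trial it leaves out the main question.
- **Section 8-3 seems to name a second quantity, an individual adherence rate, which an analysis plan might define as share of planned drug taken.** It might, but the protocol defines it nowhere, so it cannot be relied on to fill the gap.
- **Counting the actual period without the rest week is the less natural reading.** Courses are defined as 3 weeks, and the scheduled periods include every rest week. This stands: scores above 1.00 depend on an undefined term, while the cancellation does not.
- **Relative total dose has a bias of its own.** Section 5-5-1 requires stopping for recurrence, new cancer, Grade IV events and death, and Group B has longer to accrue these. This stands and shapes the fix.

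A reader might infer that early stopping would be invisible in this trial, or that a null DFS result could never be separated into longer treatment not helping and longer treatment not being given. The documents do not support that. Stopping dates, reasons and per-course dosing are all recorded, so the separation could be made from the data. A reader might also infer that every one-course stopper scores at least 100%. That holds only for a course taken in full and on time, or on the last-dose count for some partial courses.

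**Conclusion.** The point holds for the measure and its planned comparison, not for the dataset. IDI as defined is 1.00 for any number of full, on-time courses, including a Group B patient who stops at 8 of 16 with half the planned dose. If the actual period ends at the last dose, it becomes 3k/(3k − 1) and favours the earliest stoppers. The cancellation rests only on the equal planned rate in both arms and on reading the planned dose as covering all courses. The 85% and 75% group means rest on assumed shares of patients stopping.

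The flaw applies to both arms and matters more in Group B. Compliance is a secondary endpoint with no decision rule attached, and the primary DFS test in all enrolled subjects is unaffected. The change should be made because it is cheap and because the endpoint, as defined, cannot show whether the duration contrast was delivered.

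**What to change.** In sections 7-2-4 and 8-3:

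1. Add relative total dose: actual total dose divided by planned total dose over 8 courses (Group A) or 16 courses (Group B).
2. Add the proportions completing 8 and 16 courses and, in Group B, the proportion starting course 9.
3. Tabulate these by recorded reason for stopping, with recurrence, new cancer or death shown separately from toxicity or patient choice. Without this breakdown, required stops would count as non-compliance, and more so in Group B.
4. Keep IDI as on-treatment dose intensity only. Count its actual period on the same basis as the scheduled one: 3 weeks per started course, rest week included, plus delays.
5. Define or delete the individual adherence rate in section 8-3, and state the number of courses in the planned-dosage cell.
6. Name the analysis set. As worded in section 8-1, the set of all treated subjects leaves out patients who did not complete protocol treatment, so completion could not be assessed in it.

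The cost is a text change and a few extra tables. Doses per course, last dosing day and reason for stopping are already collected under sections 6-2 and 6-5.

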**7-2-5. HRQOL (Health-Related Quality of Life)/medical economics *tertiary studies conducted by participating study sites**

HRQOL and medical economics surveys were conducted at participating facilities. Models were evaluated based on collected survey data from the perspective of medical economics. Details are specified separately.

# **8. Statistical Matters (Research Evaluation Criteria and Analyses)**

## **8-1. Definition of the Target Population for Analysis**

1) All enrolled subjects: The group of all enrolled subjects excluding duplicate or invalid enrollments.

2) All eligible subjects: The group of all enrolled subjects excluding “ineligible subjects”. However, ineligible subjects are defined as subjects determined to not meet the selection criteria after enrollment, or cases in which it becomes clear that the subject meets 1 or more of the exclusion criteria.

3) All treated subjects: The group of all enrolled, qualified subjects excluding those for whom the protocol treatment was not completed.

Based on the above definitions, the main subject groups targeted for the analysis of efficacy and safety shall be all enrolled subjects and all treated subjects.

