(4) If adverse events of Grade II appear at the end of 2 weeks of capecitabine administration and recover to Grade 0–I during the 1 week off-period prescribed by the treatment protocol, “Table 3 Off-period/dose reduction criteria” does not apply, and treatment may continue without changes as deemed appropriate by the attending physician.

(5) An off-drug period should be considered during the 2 weeks of administration as a non-administration day and the administration schedule should be maintained (2 weeks on, 1 week off). Capecitabine not administered because of an off-drug period should not be re-administered. If the start of an individual treatment course is delayed, the 3-week following the start date shall constitute 1 course.

(6) If a dose reduction is performed, the dose should not be increased later.

(7) If treatment initiation is delayed for more than 3 weeks or an adverse event requiring discontinuation appears, the protocol treatment is deemed to have been discontinued.

(8) Although patient withdrawal based on self-determination is acceptable, such patients should be instructed to contact their attending physician or his/her proxy to the extent possible. The patient’s drug adherence should also be checked upon visitation.

2) The following are provisions for drug off-periods due to the occurrence of adverse events during treatment.

(1) When an adverse event of Grade I has appeared

Administration may be continued without changes.

(2) When an adverse event of Grade II or higher appears

Off-drug periods, dose reductions, and therapy reinitiation should be conducted according to “Table 3 Off-period/dose reduction criteria” below. For individual subjects, confirm the dose reduction based on the “registration confirmation form”. A single dose at the time of dose reduction and the number of single dose tablets are calculated based on “Table 4 Reduced dosages”. A single dose at the time of dose reduction is determined according to the subject’s total body surface area at the time of enrollment.

Table 3 Off-period/dose reduction criteria

|  |  | Countermeasures during treatment period | Treatment reinitiation dosages |
| --- | --- | --- | --- |
| Grade 1 |  | Off-period/dose reduction not needed | Dose reduction not needed |

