## **5-5. Treatment Discontinuation Provisions**

**5-5-1. Treatment discontinuation criteria**

If applicable, the attending physician will discontinue subsequent treatments and take appropriate measures. Investigators should observe and inspect for the evaluation items specified in “Table 6 Examination items and evaluation schedule” below at the time of discontinuation and record their findings and the accompanying rationale in their case report. In cases of termination, the attending physician shall promptly submit an administration progress survey to the study secretariat via fax.

1) When a subject him/herself withdraws consent

2) When a subject him/herself requests discontinuation of the protocol treatment

3) When recurrence of the original disease is observed

4) When novel cancerous lesions (duplicated cancer or multifocal colorectal cancer [excluding M cancer]) occurs

5) When the attending physician determines that protocol continuation will be difficult due to deterioration of comorbidities or onset of complications

6) When there is no relief or disappearance of symptoms following withdrawal due to an adverse event that falls under the off-period/dose reduction provisions (delay of treatment start by over 3 weeks or withdrawal)

7) If administration cannot be continued due to the occurrence of an adverse event even after 1 or 2 level reductions under the off-period/dose reduction provisions

8) If an adverse event of Grade IV occurs, the protocol treatment must be discontinued. (If capecitabine treatment is restarted at the discretion of the attending physician after protocol termination, a case report must be submitted.)

9) When the attending physician determines that protocol continuation will be difficult owing to an adverse event

10) If a subject dies

11) When the protocol treatment cannot be continued because the subject was transferred to a hospital

12) If a subject is determined to be ineligible after enrollment

13) Other cases in which the attending physician deems it necessary to terminate the protocol treatment

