## **8-2. Primary Endpoint Analyses**

1) The main objective of this study is to evaluate the superiority of the study drug in terms of the disease-free survival (DFS) of group B (test treatment group: 16 courses administered) compared with group A (standard treatment group: 8 courses administered). The median annual DFS for all enrolled subjects is estimated by group using the Kaplan-Meier method. Greenwood’s formula is used for interval estimation. For the evaluation of the hypothesis, the stratified log-rank test, which considers a layer composed of a combination of allocation adjustment factors excluding study sites, is used. If the one-sided significance level is 5% and it is demonstrated that group B exhibits statistically significantly superior performance compared with group A, group B will be regarded as the standard therapy replacing the group A therapy. If group B’s performance is inferior to group A, the standard therapy will remain unchanged.

2) The stratified Cox proportional hazard model will be used. This model considers the layer composed of the combination of allocation adjustment factors other than study site as an estimate of the treatment effect. The hazard ratio of the treatment effect among the groups and its 95% confidence interval will also be obtained. A Wald-type estimator is used to estimate confidence intervals. If necessary, in addition to the allocation adjustment factor, an adjusted hazard ratio accounting for background bias will be derived.

3) A similar secondary analysis will be carried out for all eligible subjects.

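### Section 8-1 calls the apparent safety set all treated subjects but defines it by completion of treatment, which would remove treatment-ending toxicity from the adverse event comparison

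*Protocol*

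**What the plan says.** Section 8-1 of the protocol defines three sets: all enrolled, all eligible and all treated subjects. The third is given as "The group of all enrolled, qualified subjects excluding those for whom the protocol treatment was not completed". The section closes by saying that "the main subject groups targeted for the analysis of efficacy and safety shall be all enrolled subjects and all treated subjects", without saying which set serves which purpose.

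Section 8-2 fixes the efficacy side: "The median annual DFS for all enrolled subjects is estimated by group using the Kaplan-Meier method". All eligible subjects are kept for a secondary efficacy analysis. Section 8-3, item 3, says that "the onset frequency of adverse events in the standard treatment group and the test group will be compared", without hypothesis testing, and names no analysis set.

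The rules that end protocol treatment are in sections 5-4-2 and 5-5-1. Three of the criteria in 5-5-1 read:

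- Item 8: "If an adverse event of Grade IV occurs, the protocol treatment must be discontinued".
- Item 7: "If administration cannot be continued due to the occurrence of an adverse event even after 1 or 2 level reductions".
- Item 9: "When the attending physician determines that protocol continuation will be difficult owing to an adverse event".

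The same list includes death and a finding of ineligibility after enrollment. Section 5-4-2 also counts treatment as stopped in two situations: "If treatment initiation is delayed for more than 3 weeks or an adverse event requiring discontinuation appears, the protocol treatment is deemed to have been" (the quote breaks off before the final word of the sentence). Table 3 stops treatment, with no restart dose, at the 4th Grade 2 onset, the 3rd Grade 3 onset and any Grade 4 event.

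**The concern.** A safety set should contain everyone exposed to the drug. Here membership depends on reaching the end of treatment, and toxicity is one of the main reasons for not reaching it. The set is therefore selected on the outcome that it is meant to describe.

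This matters more than usual because the groups differ only in planned duration, 8 against 16 courses. Adverse event frequency and severity is a named secondary endpoint. Under section 8-2 a positive DFS result would make the longer treatment the standard. A reader of the final report would need a sound account of the toxicity of the added eight courses, and the set as worded cannot supply one.

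**Working it through.** The protocol states no figure on this point, so there is nothing to reproduce. The check is a reading of the rules against each other, followed by illustrations under assumed rates.

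**Step 1. Which set serves safety.** Section 8-1 lists efficacy then safety, and all enrolled then all treated subjects. Section 8-2 puts DFS on all enrolled subjects. Taking the pairs in order leaves all treated subjects for safety. No other section assigns safety a different set.

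**Step 2. Who leaves that set.**

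| Situation | Rule | In the set as worded? |
|---|---|---|
| Grade IV event before the last planned dose | 5-5-1 item 8; Table 3 | No |
| 4th Grade 2 or 3rd Grade 3 onset | Table 3 | No |
| Delay of more than 3 weeks | 5-4-2; 5-5-1 item 6 | No |
| Adverse event stop after reductions, or on physician judgment | 5-5-1 items 7, 9 | No |
| Death on treatment | 5-5-1 item 10 | No |
| Took drug, later found ineligible | 8-1 (only qualified subjects); 5-5-1 item 12 | No |
| Grade IV event after the last planned dose, within the 28-day window of 6-2 | none applies | Can stay |

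**Step 3. How many leave (illustration).** Inputs from the protocol: 600 patients per group; 8 and 16 courses. Assumed: a constant stopping probability q per course. Proportion kept = (1 − q)^courses.

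| q | Group A kept | Group B kept |
|---|---|---|
| 2% | 0.98^8 = 85% (510 of 600) | 0.98^16 = 72% (434 of 600) |
| 3% | 0.97^8 = 78% (470) | 0.97^16 = 61% (369) |
| 5% | 0.95^8 = 66% (398) | 0.95^16 = 44% (264) |

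**Step 4. Treatment-ending events (illustration).** Assume a Grade IV probability g per course and, for simplicity, no other stopping. Patients with any Grade IV event among all dosed = 1 − (1 − g)^courses.

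| g | Group A | Group B |
|---|---|---|
| 0.2% | 1.6% | 3.2% |
| 0.5% | 3.9% | 7.7% |
| 1% | 7.7% | 14.9% |

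The set as worded would show about 0% in both groups, apart from events after the last planned dose. The difference is hidden, not reversed.

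**Step 5. Events that do not stop treatment (illustration).** Assume an event probability e = 3% per course and an independent stopping probability q = 3% at the end of each course.

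- Completers, 1 − (1 − e)^courses: A 1 − 0.97^8 = 21.6%; B 1 − 0.97^16 = 38.6%. Gap about 17 points.
- All dosed, e × [1 − r^courses] / (1 − r), with r = 0.97 × 0.97 = 0.9409: A 0.03 × (1 − 0.9409^8) / 0.0591 = 19.6%; B 0.03 × (1 − 0.9409^16) / 0.0591 = 31.6%. Gap 12 points.

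Here the completers set makes Group B look worse than the set of all dosed patients does, because every completer in Group B has the full 16 courses of exposure.

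**The case against.** The strongest reply is that this is a wording slip and not a design choice. The label says treated, and the English text has other apparent slips, such as an eosinophil threshold among the treatment criteria in 5-4-1 and a follow-up interval in 6-3 that runs to postoperative day 3. If the intended phrase was treatment not started, the toxicity exclusion disappears. That is plausible, and a reader should not infer that the sponsor chose a completers analysis. But nothing in the protocol corrects the sentence, and an analyst who followed it would exclude the wrong patients. The restriction to qualified subjects would also remain under that reading.

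Second, the assignment of this set to safety is inferred, since the closing sentence of 8-1 lacks the word respectively. This stands as a limit, although the in-order reading is the only one that fits 8-2 neatly.

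Third, a reader might infer that the set systematically favours the longer treatment, because finishing 16 courses is the harder filter. The protocol does not support that as a general statement. It holds in the sense that an excess of treatment-ending events in Group B would be hidden. For events that leave treatment running, the direction can reverse, as step 5 shows.

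Fourth, the damage is bounded. The DFS decision rests on all enrolled subjects. Urgent reporting of deaths and Grade 4 events (section 9), committee review and central monitoring (section 14) are not limited to this set. All of that stands, but none of it repairs the between-group comparison in 8-3.

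**Conclusion.** The definition is wrong as worded and must be corrected. Its label and content contradict each other. Followed literally, it would nearly empty the adverse event comparison of treatment-ending toxicity in both groups, and it would also drop dosed patients later found ineligible. The resulting comparison is unreliable, with a direction of error that depends on whether the event ends treatment.

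The exclusion itself follows from the protocol's rules, given the in-order reading of 8-1 with 8-2. Its size does not: the protocol gives neither stopping nor event rates, so the patient counts and percentages above are illustrations under constant per-course rates. The fault lies in the analysis set and not in data capture. The DFS analysis is not affected.

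**What to change.** In section 8-1, replace the third definition with: all enrolled subjects who received at least one dose of capecitabine, regardless of eligibility or completion of protocol treatment, analysed by assigned group. In the closing sentence, state outright that efficacy uses all enrolled subjects and safety uses this set.

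The cost is a rewording of two sentences. No new data are needed, because section 6-2 already collects the worst grade per course and follows adverse events to 28 days after the last dose, without limiting this to completers. Separate tables for courses 1–8 and 9–16 would be informative but are optional.
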